### Identification and determination of eligible patients

All women aged 35-80 years whom present with symptomatic moderate to severe, according to the Sandvik severity index (≥ 3) [14], predominant stress urinary incontinence, will be considered for inclusion. They should present themselves with the problem of incontinence to their general practitioner, gynaecologist or urologist. They should not have already been referred for specialised pelvic floor muscle training.

The predominance of SUI is assessed with the Stress/Urge Incontinence Questionnaire (S/UIQ). Two questions are asked. "How many times in the last seven days have you had an accidental leakage of urine onto your clothing, underwear, or pad?".

- During an activity such as coughing, sneezing, laughing, running, exercising or lifting? Symptom of stress urinary incontinence (SUI).

- With a sudden strong need to pass water that you could not reach the toilet in time? Symptom of urge urinary incontinence (UUI).

For predominant stress urinary incontinence the number of SUI events should outnumber the number of UUI.

Urodynamic testing will not be used in this study, unless the physician decides this is necessary. Its sensitivity, specificity and predictive value for diagnosing and predicting outcome in female urinary incontinence has not been proved.[15] So no exclusion criteria will be based on urodynamic assessments (if performed).

SUI must have been demonstrated on physical examination or on urodynamic assessment if performed. Patients will be excluded in case of previous incontinence surgery, pelvic organ prolaps stadium 2 or higher according to POP-Q classification or in case of residual post voiding bladder volume of more than 100 ml on catheterisation or ultrasound (Bladderscan^®^)

### Study Interventions

After obtaining informed consent, eligible women will be assigned to either PFMT by a specialised physiotherapist for a standard of 9-18 sessions in a period of 6 months, or TVT(O) surgery.

### Randomisation

After checking the inclusion criteria an eligible patient is asked if she might be willing to participate and will receive written and verbal information about the study. A new appointment with the research nurse will be made. After an interval of one week the research nurse will ask if the patients wants to participate in the study and the exclusion criteria are checked. This will be done by the research nurse, not by the medical specialist him/herself. If an eligible patient wants to cooperate she is asked to sign the informed consent. When in- and exclusion criteria are met, randomisation will take place. Study inclusion and exclusion criteria are presented in figure 2.

**Figure 2 F2:**
[figure not shown]
**Study inclusion and exclusion criteria**.

Randomisation will be performed with the use of computerised randomisation tables. The randomisation will be stratified according to the severity of incontinence (moderate or severe as established by the Sandvik index. For obvious reasons (surgery versus conservative treatment) both the randomisation outcome and the personal involved in outcome assessment cannot be blinded.

### Patient follow-up procedures

Patients will be followed from the start of primary therapy until 18 months later. Follow up will consist of various elements

In all patients the next items will be recorded at inclusion:

1. Baseline characteristics

2. History and clinical examination

3. 48 h-bladder (voiding and incontinence) diary

4. 24 h-padtest

5. Validated Quality of Life questionnaires (Urinary Distress Inventory, Incontinence Impact Questionnaire, Euroqol 5D, patient global impression of severity/improvement)

6. Uroflow measurement including post void residual volume

7. Cost-analysis questionnaire

The onset of primary therapy, either TVT(O) in the surgery arm of the study or PFMT in the physiotherapy arm of the study will be T = 0

In case of surgery, the patient will receive the standard care associated with the pre-, per- and postoperative standards of the participating hospital. She will visit the hospital after surgery at 6 weeks, 6, 12 and 18 months. Questionnaires will be handed out at these visits containing the items mentioned above. Furthermore, special attention will be given with respect to extra visits to the general practioner, physiotherapist or specialist visits in relation to the surgical procedure that might have taken place and physical examination will be performed. Costs associated with incontinence and therapy will also be assessed with telephone administered questionnaire at 2 and 4 months follow-up. Women who are enrolled for PFMT will be followed-up according to the same schedule besides the 6 weeks post operative check-up.

### Patient outcome measures

This study will compare the clinical and cost-effectiveness of PFMT versus the TVT/TVT-O procedure as treatment for moderate to severe stress urinary incontinence.

Primary outcome: Subjective improvement of urinary incontinence

Secondary outcome(s):

1. Complete cure on objective and subjective parameters.

2. Subjective improvement in generic and disease-specific quality of life.

3. Complications and de novo urogenital symptoms.

4. The incremental cost-effectiveness of TVT as compared to PFMT, accounting for direct and indirect costs parameters.

5. Development of a prediction model for successful treatment, with the therapy given (PFMT or TVT) as independent variable in the model.

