## Abstract

**Background:**

Stress urinary incontinence is a common condition affecting approximately 20% of adult women causing substantial individual (quality of life) and economic (119 million Euro/year spent on incontinence pads in the Netherlands) burden. Pelvic floor muscle training (PFMT) is regarded as first line treatment, but only 15-25% of women will be completely cured. Approximately 65% will report that their condition improved, but long term adherence to treatment is problematic. In addition, at longer term (2-15 years) follow-up 30-50% of patients will end up having surgery. From 1996 a minimal invasive surgical procedure, the Tension-free Vaginal Tape (TVT) has rapidly become the gold standard in surgical treatment of stress urinary incontinence. With TVT 65-95% of women are cured. However, approximately 3-6% of women will develop symptoms of an overactive bladder, resulting in reduced quality of life. Because of its efficacy the TVT appears to be preferable over PFMT but both treatments and their costs have not been compared head-to-head in a randomised clinical trial.

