In the past decade, surgery for stress incontinence has made a huge progression with the introduction of minimally invasive surgical techniques. The Tension-free Vaginal Tape (TVT) and Tension-free Vaginal Tape Obturator (TVT-O) are the most frequently performed procedures. In both cases, a small incision is made under the mid urethra through which a polypropylene mesh is placed without tension under the urethra. If abdominal pressure increases, the urethra is compressed to the tape and continence is restored. An advantage of these procedures is that they can be performed in day-care.[8] After a TVT(O) procedure approximately 66% of women are completely cured (100% dry) and 80-95% of women show an improvement.[9] Furthermore, this effect seems to be longstanding. However, although minimal invasive, stress incontinence surgery carries a risk of complications. Major complications are extremely rare with an incidence of 0.007% for bowel perforation and 0.012% for vascular injury.[8] The most common complication of bladder perforation during the procedure (approximately 3-6% for TVT and below 1% for TVT-O is easily recognized during the procedure itself and carries no long-term morbidity. Adverse outcome of surgery in terms of the development of new symptoms may be a bigger concern. Voiding difficulties and symptoms of an overactive bladder are reported in 6% of cases.[9]

In the Netherlands, women are usually seen by the general practitioner (GP) first. The GP Dutch guidelines (revised version 2006) on stress incontinence advocate to either start treatment with PFMT with instructions of the GP, or to refer to a specialised physiotherapist. In 2001 the Health Counsel reported that only 1.6% of women were referred to a physiotherapist.[10] Thus, the majority of incontinent women were not referred to specialised therapy. Treatment by the GP consists of giving verbal and written instructions (as is described in their guideline) how to contract and train the pelvic floor, with first revision after 3 months. This is clearly different from the weekly, individual sessions given by a specialised (biofeedback) physiotherapist. If treatment by the GP fails, it is advocated to refer the woman for specialised PFMT physiotherapy. This is the group of women where our study aims at.

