### Statistical analysis

Data will be presented as numbers (percentage) for nominal variables or means (standard deviation) for interval variables. Differences between the two interventions will be analysed based on intention-to-treat analysis. For interval variables, differences between the two groups will be analysed with a Students t-test, proportions will be compared using the Chi-square test.

Multivariate logistic regression analysis will be used for the development of the prediction of successful treatment only. In literature, a wide range of patient characteristics were considered to be associated with the outcome of PFMT. In the Consultation on Incontinence (ICI) proceedings it was concluded that there are no reliable factors identified yet, because the number of observations and studies is too low.[2] However, several factors have been identified as possible predictors of a successful outcome after PFMT. To provide information on treatment effectiveness in different subgroups of patients participating in this trial, we will derive a prediction model and estimate interaction of treatment effect with baseline incontinence severity (number of leaks/week), duration of symptoms, increasing parity, Body Mass Index, baseline pelvic floor contraction ability, and treatment modality as factors.[2] The defined prediction model will therefore be pre-specified resulting in less over-optimism than models in which the choice of predictors is strongly driven by the data-set and the need for external validation.[19] From the multivariate logistic model, in which success will be defined as cure (no objective or subjective incontinence) at 12 and 18 months follow-up, we will estimate the weight of the different coefficients. The modelling process will be internally validated by bootstrap resampling. This technique gives an impression of how "over-optimistic" the model is i.e., how much the performance of the model may deteriorate when applied to a new group of similar patients.[20]

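### Secondary outcome 3 counts only new urogenital symptoms, so worsening of urge leakage that women may already have at entry has no place in the harm outcome

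*Protocol article*

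**What the plan says.** All references are to the protocol article.

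- **Harm outcome** (Patient outcome measures, secondary outcome 3): "Complications and de novo urogenital symptoms". Worsening of a symptom already present is not mentioned.
- **Entry rule** (Identification and determination of eligible patients): "For predominant stress urinary incontinence the number of SUI events should outnumber the number of UUI". The count covers the last seven days.
- **Exclusions in the same section**: "Patients will be excluded in case of previous incontinence surgery, pelvic organ prolaps stadium 2 or higher according to POP-Q classification", and a post-void residual above 100 ml. None concerns urge or overactive bladder symptoms. Figure 2, which lists the criteria, is not shown.
- **Why the harm matters**: the abstract says that after the tape "approximately 3-6% of women will develop symptoms of an overactive bladder, resulting in reduced quality of life". The Background section says "Adverse outcome of surgery in terms of the development of new symptoms may be a bigger concern" and then "Voiding difficulties and symptoms of an overactive bladder are reported in 6% of cases".
- **Analysis** (Statistical analysis): "Differences between the two interventions will be analysed based on intention-to-treat analysis"; interval variables are compared by t-test, and "proportions will be compared using the Chi-square test". No denominator is set for the de novo outcome.
- **Schedule** (Table 2 and footnote): surgical complications are ticked in the 2 and 4 month column only, and the footnote confines them to surgery. The UDI is taken at baseline, 6, 12 and 18 months, and the 48-hour bladder diary at baseline, 6 and 12 months.

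**The concern.** The entry rule and the harm outcome do not fit together. Entry tolerates urge leakage, provided that it is the lesser component. The outcome meant to capture the urogenital downside of surgery then counts a symptom only if it was absent before.

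Take a hypothetical woman with 10 stress and 8 urge leaks in the week before entry. She is eligible. If surgery cures the stress leaks and her urge leaks double to 16, she has had the kind of harm that the background warns about, yet her urge leakage is not de novo.

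The Knowledge transfer section says the results should inform whether pelvic floor muscle training (PFMT) remains the primary treatment for every patient. That judgement sets an expected gain in improvement (65% against 80%) against the harms of surgery. A harm outcome that leaves out deterioration in women with mixed symptoms gives an incomplete account of that second side.

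**Working it through.** **1. The plan's own figure.** The article gives no sample size or power for outcome 3. Its one sample size is for improvement, 65% against 80%, power 0.9, alpha 0.05:

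n = [1.96 × √(2 × 0.725 × 0.275) + 1.2816 × √(0.65 × 0.35 + 0.80 × 0.20)]² / 0.15² = 185 per arm, or 198 with continuity correction.

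That reproduces the stated 200. The harm outcome plays no part in it, so this point leaves it untouched.

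**2. Can a woman with urge leakage enrol?** Yes. The condition is stress events > urge events, which allows urge events above zero. A rule comparing the two counts has work to do only if some women have both.

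**3. Does outcome 3 have a place for worsening?** It has two parts.

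- *De novo symptoms.* By meaning, these exclude a symptom present at baseline.
- *Complications.* The footnote to Table 2 restricts these to surgery, so they are not a two-arm measure. The table ticks them at 2 and 4 months, not at 6, 12 or 18. The follow-up section also asks at visits about extra care linked to the operation, but that records use of care, not symptoms.

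**4. Would another outcome count it as harm?** The abstract assigns the UDI to quality of life, and secondary outcome 2 frames that as improvement. As an interval score it would be compared by t-test. If a share m of an arm worsens by b points while the rest improve by a points, the mean improvement is (1 − m) × a − m × b. This is positive whenever a/b > m/(1 − m). A mean benefit is therefore compatible with a harmed minority, and the comparison does not show how many women were harmed.

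**5. How large is the gap?** Women per arm whose worsening outcome 3 omits = 200 × f × w, where f is the share with urge leakage at baseline and w the share of those who worsen. The article gives neither. As pure assumptions:

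| f | w = 5% | w = 10% | w = 20% |
|---|---|---|---|
| 20% | 2 | 4 | 8 |
| 40% | 4 | 8 | 16 |
| 60% | 6 | 12 | 24 |

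The spread from 2 to 24 only returns what was put in. It shows that the size cannot be derived from the article, and no cell is an estimate.

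**The case against.** **The harm can surface elsewhere.** The primary outcome concerns urinary incontinence as a whole, and the prediction model defines cure as no objective or subjective incontinence. A woman whose urge leakage doubles is not cured and may report no improvement. UDI effects are to be reported separately. This stands: it would be wrong to say that worsening goes unrecorded in the trial. But failing to improve or be cured pools the worsened with the unchanged, and a woman relieved of stress leakage may call herself improved overall. The gap is in the harm outcome, not in data collection.

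**Detail belongs in the analysis plan.** An article may leave the definition and denominator of a secondary outcome to documents not shown. That stands for the denominator. It does not cover the word de novo, a restriction the article itself states; adding worsening changes the outcome.

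**Figure 2 is not shown.** It might narrow entry. The number of women affected is therefore open, but the entry rule in the text plainly contemplates both kinds of leakage.

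**A stronger reading to resist.** A reader might infer that the de novo rate is diluted, because women with urge leakage sit in the denominator without being able to have the event. The documents do not support this:

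- No denominator is fixed. The intention-to-treat and chi-square sentences are general, and women free of the symptom at baseline would be a natural denominator for a de novo event.
- The 3-6% and 6% figures are not stated as rates among women at risk, and the 6% pools voiding difficulties with overactive bladder.
- Women with urge leakage can still register a new voiding difficulty, another new symptom or a complication.
- Even if all randomised women were the denominator, randomisation balances baseline urge leakage in expectation, so the ratio between arms would hold.

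**Conclusion.** The point holds as a mismatch between a stated entry rule and a stated outcome. Women with existing urge leakage may enrol, overactive bladder symptoms are named as a main concern after surgery, and outcome 3 recognises urogenital symptoms only when new. Neither the complications item, which is confined to surgery and ticked at 2 and 4 months, nor the improvement-framed UDI comparison counts women who worsen.

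Its size is unknown. The article gives no baseline share with urge leakage, no rate of worsening and no denominator for the de novo rate. The conclusion needs only that some enrolled women have urge leakage at entry and that some of them may worsen; it does not depend on which denominator is used. It concerns one secondary outcome. The sample size and the primary analysis stand, and no bias in the primary comparison is shown.

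**What to change.** Restate secondary outcome 3 as complications and new or worsened urogenital symptoms. Score the symptom part in both arms, against each woman's baseline, from the UDI (baseline, 6, 12 and 18 months) and the 48-hour bladder diary (baseline, 6 and 12 months). Report two results for each symptom:

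1. new symptoms among women free of that symptom at baseline;
2. worsening among women who had it at baseline, with the threshold for worsening fixed before the data are compared by arm.

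The article does not describe the items of the UDI or whether the diary separates urge from stress leaks. The trial team should confirm that urge and voiding symptoms can be scored separately from these instruments.

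On that footing the change needs no new visits or measurements. It costs revised outcome wording, a short scoring rule and one extra table. The downside is that the reported harm rate may be less favourable than under a de novo count alone.

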### Sample size considerations

Literature shows a subjective improvement of incontinence after PFMT up to 65%, and a subjective improvement after TVT(O) of at least 80%. In order to detect this difference with a power of 0.9 and an alpha of 0.05, we need 200 women in each trial arm. For our primary outcome parameter, total cure of incontinence, the expected difference between both arms is much larger: 28% cure after PFMT, and 65% cure after TVT. The 200 women in each treatment arm will be largely sufficient to assess a statistically significant difference in this secondary outcome.

Sample size calculation for the prediction models is based on the number of successes (or failures). For each predictor in the model we need 10-15 successes. Our pre-defined prediction model consists of 5 predictors and the interaction terms with treatment. Our total sample size will exist of 400 women. The expected number of successes (cure) of the PFMT group is 30 (15% of 200) women, the number of women cured after TVT is an estimated 130 (65% of 200 women). So the total number of complete cure is an estimated 160 women, with 240 women being not completely cured. These figures are sufficient for modelling up to 10-12 predefined possible predictors of cure. With respect to subjective improvement an estimated total of 290 women will show subjective improvement as measured with the Patient Global Impression of Improvement (PGI-I) questionnaire (65% of 200 women with PFMT plus 80% of 200 women in TVT group). Thus, 110 women can be considered failures. Again, this also allows us to make a prediction model for improvement with the predefined predictors. Therefore the study sample will also be amply sufficient for prediction purposes.

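### The plan's own event counts do not support calling the sample amply sufficient for prediction: it is adequate for cure, borderline for improvement with interactions, and thin for treatment-specific slopes

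*Protocol article*

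**What the plan says.** All of the following is in the protocol article.

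- **Sample size considerations** bases the prediction-model calculation on the number of successes or failures and sets a rule: "For each predictor in the model we need 10-15 successes".
- The same section gives the model's content: "Our pre-defined prediction model consists of 5 predictors and the interaction terms with treatment".
- It then counts events: "The expected number of successes (cure) of the PFMT group is 30 (15% of 200) women". It adds 130 cures after TVT, giving 160 cured and 240 not cured, and says this supports 10-12 predictors of cure.
- For improvement it expects 290 successes and 110 failures. It says a model with the predefined predictors is possible here too, without dividing the 110 by a number of terms. It closes with: "Therefore the study sample will also be amply sufficient for prediction purposes".
- **Statistical analysis** says the team will "estimate interaction of treatment effect with baseline incontinence severity" and continues the list with "duration of symptoms, increasing parity, Body Mass Index, baseline pelvic floor contraction ability, and treatment modality as factors". That makes five patient factors plus treatment. It defines success in the model as cure at 12 and 18 months. It uses the bootstrap for internal validation, to give an impression of over-optimism.
- The **Abstract** gives the purpose of the model as supporting individual treatment decisions in future patients.

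**The concern.** A claim of ample size implies a reserve. The section does the division only for cure, and only with both arms pooled. For improvement, which is the trial's primary outcome, the limiting group is 110 women, about two thirds of the 160 available for cure, yet the same conclusion is carried over.

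Pooling also hides where the information for the interactions lies. Individual advice between PFMT and TVT depends on how each predictor acts within each arm, and one arm is sparse for each outcome. If the reader accepts the claim as written, there is little reason to shrink coefficients or to treat interactions cautiously. Individual predictions could then look more reliable than the data allow.

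**Working it through.** **Inputs.** From Sample size considerations: 200 women per arm and 400 in total; 10-15 events per predictor; cure 15% (PFMT) and 65% (TVT); improvement 65% and 80%; a second PFMT cure rate of 28%. From Statistical analysis: five patient factors plus treatment. Assumption: one degree of freedom per predictor. Categorical or non-linear terms would lower every ratio below.

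**1. The plan's own figures.**
- Cured: 0.15 × 200 + 0.65 × 200 = 30 + 130 = 160; not cured: 400 − 160 = 240.
- Improved: 0.65 × 200 + 0.80 × 200 = 130 + 160 = 290; failures: 400 − 290 = 110.
- Predictors of cure supported: 160/15 = 10.7 to 160/10 = 16. The stated 10-12 is reproduced and means 160/12 = 13.3 to 160/10 = 16.0 events each.

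**2. Model size.** 1 (treatment) + 5 (predictors) + 5 (interactions) = 11 coefficients. The rule then needs 11 × 10 = 110 to 11 × 15 = 165 events in the smaller outcome group.

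**3. Pooled support, smaller outcome group divided by coefficients.**

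| Model | Limiting group | Coefficients | Events per coefficient |
|---|---|---|---|
| Cure, with interactions | 160 | 11 | 14.5 |
| Improvement, with interactions | 110 | 11 | 10.0 |
| Improvement, without interactions | 110 | 6 | 18.3 |

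At 15 events each, 110 failures support 110/15 = 7.3, so 7 terms. Reaching 165 failures would take 400 × 165/110 = 600 women. If the treatment main effect is not counted, the two interaction models have 160/10 = 16.0 and 110/10 = 11.0.

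**4. Loss to follow-up.** The calculation states no loss rate, so a range is assumed, with events lost in proportion.

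| Assumed loss | Cure (11 terms) | Improvement (11 terms) |
|---|---|---|
| 5% | 13.8 | 9.5 |
| 10% | 13.1 | 9.0 |
| 15% | 12.4 | 8.5 |
| 20% | 11.6 | 8.0 |

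**5. Support by arm.** Write the model as logit(p) = a + bT + Σc_j·x_j + Σd_j·T·x_j. In the arm with T = 0 the slopes are c_j; in the arm with T = 1 they are c_j + d_j, with intercept a + b. No parameter is shared, so an unpenalised fit is identical to two separate fits. Each d_j is the difference between two arm-specific slopes, and the sparser arm limits its precision. With five slopes per arm:

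| Outcome | Arm | Smaller group | Events per slope |
|---|---|---|---|
| Cure | PFMT, 15% | 30 | 6.0 |
| Cure | PFMT, 28% | 56 | 11.2 |
| Cure | TVT | 70 | 14.0 |
| Improvement | PFMT | 70 | 14.0 |
| Improvement | TVT | 40 | 8.0 |

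At 28% the pooled cure count is 56 + 130 = 186, or 186/11 = 16.9 per coefficient.

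**The case against.** The strongest reply is that the plan keeps its own rule. The rule is stated for successes or failures overall, and on 11 coefficients neither model falls below 10. A reader might infer from the word *amply* and the interaction terms that the model fails the plan's rule. It does not, and no sum in that section's prediction paragraph is wrong. **This stands.**

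A reader might also treat 6 and 8 events per slope as a breach. The plan states no within-arm rule; applying one is a statistical extension. **This stands.** The equivalence to two arm-specific models is an algebraic fact, however, so the extension is the relevant count for treatment-specific advice.

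The improvement model may not include interactions at all. The sentence on improvement mentions only the predefined predictors, and Statistical analysis defines model success as cure. On that reading support is 18.3 and comfortable. **This stands as an alternative reading**, and the point on improvement is conditional on it.

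The PFMT shortfall for cure depends on the 15% rate. **This stands:** at 28% it disappears. The Background quotes 15 to 28% as a range, and each end is the cautious choice where it is used: 28% shrinks the expected difference in cure, and 15% shrinks the event count. The section does not say so. The TVT figure for improvement does not depend on this choice.

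Finally, the predictors are pre-specified and the bootstrap measures optimism. Both are real safeguards. **This stands in part:** as described, the bootstrap reports over-optimism, and the article does not say the coefficients will be corrected for it. An unseen analysis plan may do so, and the article's silence on that detail is not itself the finding.

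**Conclusion.** The point holds as an overstatement in the sufficiency claim. It does not show an arithmetic error or a broken rule. On 11 single-degree-of-freedom coefficients, pooled support is 14.5 for cure, within the rule, and 10.0 for improvement, at its floor and without reserve. Treatment-specific slopes are thin: about 6 events per slope for cure after PFMT at the 15% rate (11.2 at 28%) and 8 for improvement after TVT.

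The conclusion on improvement assumes that its model carries the interactions. The conclusion on cure after PFMT assumes the 15% rate.

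A reader might go further and conclude that the predictions will be badly miscalibrated by some stated amount. The documents do not support a figure, because that depends on predictor effects that they do not give. Overfitting in the sparse arms is plausible, but its size here is unknown.

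Severity is minor. The prediction model is the fifth-listed secondary outcome, and the primary comparison of the two arms is unaffected.

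**What to change.** 1. In Sample size considerations, replace the closing claim with wording such as: *sufficient by the rule for cure, borderline for improvement with interactions, weak for arm-specific effects*. Give events per coefficient, pooled and by arm, and say whether the improvement model includes interactions.
2. Reconcile the 15% and 28% PFMT cure rates, or state that they are the two ends of the range in the Background and why each is used where it is.
3. Keep all pre-specified terms, but fit with penalisation (for example ridge) or apply the bootstrap-estimated shrinkage to the coefficients. Penalising the interaction terms pulls the two arms' slopes towards each other, so the sparse arm borrows from the fuller one.
4. Label the interactions exploratory.

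The cost is wording and a different fitting option, with no extra patients or data. The downside is that interaction estimates are pulled towards zero, so a real difference between arms would be understated, and the sufficiency statement becomes less favourable.
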